## Abstract

**Background:**

Patients with stroke frequently experience walking dysfunction. Core training can help improve balance and walking function in patients with stroke. However, core training movements in clinical practice are numerous and differently targeted. Therefore, this study will investigate the improvement of walking function in patients with combined diaphragmatic breathing maneuver (DBM) and draw-in breathing technique (ADIM) training.

**Methods:**

This single-blind, randomized controlled preliminary will analyze the viability of DBM combined ADIM training versus routine rehabilitation therapy in patients with stroke with early to mid-stroke. Patients will be randomly assigned to either the DBM and ADIM training or the routine rehabilitation training. We will recruit 42 stroke inpatients from the Second Rehabilitation Hospital of Shanghai who meet the trial criteria and measure the balance and walking functions and improvement of that after 4 weeks of intervention. The primary outcome is the 10 m maximum walking test (10MWT). The secondary outcomes indices include the limits of stability test (LOS), Berg balance scale test (BBS), Functional Ambulation Categories test (FAC), Timed Up and Go test (TUG), trunk impairment scale test (TIS), ultrasound indicators of the diaphragm and transversus abdominis (UI), rhythmic weight shift test (RWS), walk across test (WA), Fugl-Meyer assessment of lower extremity (FMA-LE), and Barthel index of ADL test.

**Discussion:**

The primary objective of this project was to investigate the effects of DBM combined with ADIM on balance capacity and walking function for patients with early to mid-stroke. The outcomes of this study will hold significant implications for future clinical applications in rehabilitation.

**Trial registration:**

Chinese Clinical Trial Registry (ChiCTR), ID: ChiCTR2100054897. Registered on 28 December 2021.

**Supplementary Information:**

The online version contains supplementary material available at 10.1186/s13063-023-07690-6.

## Introduction

### Background and rationale {6a}

Stroke is an acute neurovascular disorder caused by inadequate blood supply to the brain; it has the characteristics of long duration, wide range, and severe degree. These conditions can dramatically limit a patient’s quality of life (QoL) and ability to manage activities of daily living (ADL) [1]. It has become the second leading cause of death and the third leading cause of disability worldwide, with an estimated incidence of 25% over a lifetime [2]. In recent years, with the acceleration of rescue speed and the improvement of thrombolysis technology, the mortality rate of patients with stroke decreased significantly. However, due to the advanced age of the patients and the uneven development between rehabilitation medicine and clinical medicine, the recovery process for central nervous system injuries tends to be protracted. Stroke has become the most common cause of long-term disability in adults [3]. While 50–70% of stroke patients regain functional independence, 15–30% will experience permanent disability, contributing significantly to social and economic burden by 2020 [4]. The World Health Organization speculates that about 75% of the lives of people with disabilities worldwide are related to the benefits of rehabilitation, so stroke rehabilitation requires urgent international attention [2].

Walking, as a fundamental activity of daily living (ADL), plays a pivotal role in the well-being and overall health of older individuals. However, following an early stroke, a study found that 63% of patients were unable to walk independently, and even after clinical and rehabilitation efforts, 22% remained unable to walk [5]. This disease severely restricts patients’ daily activities and social participation, greatly impacting their quality of life. Existing research predominantly focuses on rehabilitating lower limb function in hemiplegic patients, neglecting the importance of trunk control in walking recovery. However, as early as 1992, Wagenaar et al. began to observe the relationship between trunk and gait in patients with stroke [6]. By 2002, studies have shown that trunk control is related to walking function parameters such as walking speed, walking distance, and balance [7]. In 2006, Verheyden et al. evaluated trunk function with a trunk control test, trunk injury scale, Tinetti balance and gait subscale, functional walking classification, 10-m walking test, timing take-off test, and functional independence exercise scale. It was found that trunk function was significantly correlated with balance, gait, and walking ability [8]. Further investigations highlighted the influential role of core muscle strength on balance and walking function [9]. In recent years, several investigations have revealed that incorporating core stability training or respiratory training in interventions can enhance the activation of core muscles, promote trunk stability, and subsequently improve lower limb movement control, walking speed, and other aspects of ambulatory function [10, 11]. There exists a strong correlation between trunk stability and human ambulatory function. Thus, for the impairment of walking function, the treatment of core muscles cannot be ignored.

Currently, the training of core strength for patients with stroke mainly includes central intervention techniques based on repetitive transcranial magnetic stimulation (rTMS) and peripheral intervention training based on Bobath methods and core stability training. However, the high cost and difficulty in locating the core muscles make rTMS inaccessible for widespread use in rehabilitation institutions. Additionally, the time-consuming nature of various clinical core strength training methods often leads to patient fatigue. In addition, there is a need for a rehabilitation technique that requires less time and provides precise targeting of core stability. Furthermore, to investigate that, we want to accurately measure the change in core muscles and evaluate the parameters related to trunk balance and walking function after intervention.

Diaphragmatic breathing maneuver (DBM) is a slow, deep, and regular breathing training that consciously extends the time of inhalation and exhalation and focuses on abdominal ups and downs [12]. In recent years, regarding the effect of DBM on the walking function of patients with stroke, most studies mainly focused on walking endurance [13]. It is worth noting that DBM can effectively stimulate the core muscles by activating diaphragmatic muscle contraction, increasing intra-abdominal pressure, achieving the effect of stabilizing the spine, and improving the core stability of patients with stroke [14].

The draw-in breathing technique, also known as the abdominal drawing-in maneuver (ADIM), is a method that specifically engages the transversus abdominis muscle before activating other abdominal muscles. This technique plays a crucial role in stabilizing spinal segments. It is commonly used to enhance the lumbar spine and pelvic stability by restoring transversus abdominis and internal abdominal obliques. In 2015, Lee et al. provided the first evidence to highlight the positive effects of ADIM training on core and postural stability in non-athletes with core instability [15]. Since then, research into the effects of ADIM on trunk stability has begun to receive attention. Research has indicated that incorporating ADIM movements into bridging exercises leads to the enhanced strengthening of the abdominal muscles and improved trunk stability compared to performing bridging exercises alone [16]. Moreover, ADIM training has been found to improve gait parameters and reduce pain symptoms in patients with lower back pain, resulting in pain reduction and improved gait symmetry [17]. These suggest that ADIM can improve trunk stability and walking function. In recent years, ADIM combined with bridging/pelvic training is effective in improving trunk stability in patients with stroke; however, the benefits of ADIM in improving walking function in patients with stroke are unclear [18, 19].

### Objectives {7}

DBM and ADIM target different trunk muscle groups, but the main trunk muscle groups activated by the two exercises are complementary, and it is not known whether DBM combined with ADIM can improve trunk stability and thus further promote walking function. It is therefore important to identify the site of action of the technique on the trunk, to investigate the mechanism of its effect on trunk stability in patients with stroke, and to observe the effect of the technique on further walking function.

### Trial design {8}

To evaluate the efficacy of combining DBM with ADIM in patients with stroke, a randomized controlled trial utilizing a parallel design and employing an assessor-blinded methodology will be conducted. Participants are all inpatients of the Neurorehabilitation Department of Shanghai Second Rehabilitation Hospital who correspond with the inclusion criteria. The research projects are registered with the Chinese Clinical Trials Registry (ChiCTR-2100054897), and the study has been approved by the Ethics Committee of the Shanghai Second Rehabilitation Hospital (Shanghai, China). All participants will be informed of the trial and will sign a written informed consent form.

Patients who meet the inclusion criteria will be randomly grouped after basic data collection. This will be done by using a computer-generated random number table to randomly divide the subjects into a control group (receiving 4 weeks of conventional rehabilitation without other specific exercise interventions), and a study group (receiving 4 weeks of DBM + ADIM intervention alongside conventional rehabilitation) in a 1:1 ratio. Random numbers will be placed in opaque envelopes by independent persons not involved in this experiment to achieve allocation concealment. As this study uses an exercise intervention, it will be difficult to conceal the grouping from the therapist and subjects, but it will be possible to blind the outcome indicator measurer. We will arrange for a new assessor to replace the assessor familiar with allocation to achieve single blinding.

In this trial, a superiority trial framework has been established to examine a specific core training approach, with the aim of improving walking function in patients with stroke. The trial process includes an initial assessment one week before the start date, a final assessment post-trial, and a follow-up evaluation six months later. These evaluations serve the purpose of measuring treatment effectiveness, assessing potential side effects, and documenting relevant baseline data and clinical information of the participants. The study procedure is shown in Fig. 1 and the period of the study in Fig. 2. The program follows the principles of SPIRIT 2013.

**Fig. 1 Fig1:**
[figure not shown]
Flow chart of the study

**Fig. 2 Fig2:**
[figure not shown]
The schedule of enrolment, interventions, and assessments

## Methods: participants, interventions, and outcomes

### Study setting {9}

All subjects will be recruited from the Second Rehabilitation Hospital of Shanghai. Treatment of patients will be carried out in the sports rehabilitation treatment unit of the hospital. Physiotherapists will provide rehabilitation treatment to all patients, including ADIM, DBM, and traditional rehabilitation, in strict accordance with the requirements of the trial and ethical standards.

### Eligibility criteria {10}

#### Inclusion criteria

Age between 40 and 85 years;Consistent with a diagnosis of cerebral hemorrhage or cerebral infarction;The level of Brunnstrom lower limb classification greater than III;Course of disease 1 year;Clear consciousness, no intellectual impairment, Modified Mini-Mental State Examination score (MMSE) more than 24;Patients have signed an informed consent form.

#### Exclusion criteria

Patients with serious illness or in the acute stage of illness;Those who with severe cognitive and verbal impairment or inability to cooperate;Those who with Parkinson’s, spinal cord injury, or other conditions affecting trunk stability;Those who with severe visceral organ disease;Those who with specialized sports training.

### Who will take informed consent? {26a}

Trained research nurses will conduct the trial introduction, utilizing a comprehensive video presentation to highlight the key aspects of the study. In addition, patients will receive informative sheets. Research nurses will provide detailed discussions on the trial with patients, based on the information presented in the video and sheets. Thereafter, patients will be facilitated for an enlightened engagement with the attending consultant. Written consents from the patients choosing to participate in the trial will be obtained by the research nurses. Subjects will be given informed consent prior to the trial being conducted and written documentation will be shown in the Supplementary material.

### Additional consent provisions for collection and use of participant data and biological specimens {26b}

The study was carried out with full protection of subject rights and medical ethics in mind. Its main aim was to observe the improvement of patients’ walking ability through core training. None of the test indicators necessitated the collection of specimens from the subjects. In line with legal and ethical obligations, the trial will be overseen by independent entities such as the trial steering committees and data monitoring committees, ensuring the protection of subjects’ rights throughout the process. The arbitrary collection and utilization of subject data for other ancillary studies can complicate trial implementation and give rise to ethical and legal issues. Given this, there is no need for the collection and usage of subject data and biospecimens for other ancillary studies in this trial.

## Interventions

### Explanation for the choice of comparators {6b}

Physiotherapy for patients with stable early to mid-stroke vital signs who in keeping with the inclusion criteria, with reference to the routine rehabilitation program developed by the therapist in the *2017 edition of the Chinese Guidelines for Early Stroke Rehabilitation* and the *2019 edition of the Chinese Clinical Management Guidelines for Cerebrovascular Diseases (Abridged Version)—Stroke Rehabilitation Management*. The patients in the control group will undergo regular rehabilitation as described in item 11a.

### Intervention description {11a}

Control group (CG)Patients in the control group will receive routine rehabilitation training. Routine rehabilitation training will include (1) motor therapy and functional training for hemiplegic limbs; (2) sitting and standing balance training; (3) weight transfer training; (4) walking training; (5) and ADL training, among others. The therapist will inform the patient of the training prior to carrying out the rehabilitation. The duration of the regular rehabilitation will be 60 min five times a week for four weeks. All interventions for the control group will be carried out by three experienced intermediate therapists separately.Study group (SG)In addition to receiving the same type of routine rehabilitation as the control patients, patients in the study group will also be required to undergo DBM and ADIM sessions. Each rehabilitation session for patients in the trial group will be divided into 40 min of regular rehabilitation and 20 min of DBM combined with ADIM training. The study group will complete 5 training sessions per week for 4 weeks in the same setting. All interventions for the study group will be delivered separately by three experienced intermediate therapists.

#### DBM training

Instruct the patient to lie in a supine position with the knees and hips in a slightly flexed and comfortable position. Instruct the patient to do a deep inhalation and consciously puff out the abdomen, pause briefly after a full inhalation, and hold this position for 10 s. This is followed by a slow exhalation with a conscious retraction of the abdomen on the exhalation, in a slow and deep rhythm. To ensure that the patient performs the exercise correctly, ask the patient to place one hand on the chest and the other on the abdomen. The patient is also advised to breathe deeply so that he or she only the hand on the abdomen is felt to be moving and not the hand on the chest. The DBM training is performed in 3 sets of 10 reps each and rests 1 min between sets. The workout is limited to 10 min.

#### ADIM training

Prior to the intervention, the therapist will receive a training session on the operation of ADIM training. The subject is positioned supine with the hips flexed at 40–60° and the knees flexed at 90–100°, with the arms resting on the trunk. Instruct the patient to delicately retract the navel towards the spine, maintaining a contracted abdomen while engaging in regular breathing. The successful contraction of the transversus abdominis muscle is defined as the sustained presence of progressive deep tension in the abdominal wall for a duration of 10 s. At this time the therapist can palpate the muscles on the medial aspect of the anterior superior iliac spine that are contracting. Patients who present with either of the compensatory patterns of posterior pelvic tilt, or downward heel pressure, will be considered non-compliant for this movement. The ADIM training is performed in 3 sets of 10 reps each and rests 1 min between sets. The workout is limited to 10 min.

### Criteria for discontinuing or modifying allocated interventions {11b}

The patient’s rehabilitation will be carried out under continuous and strict heart rate monitoring. The criterion for termination of exercise is an increase in the patient’s heart rate to more than 80% of their heart rate reserve. Furthermore, any adverse events such as dizziness, extreme dyspnea, or chest pain experienced by the patients will be promptly recorded by the therapist. These events will then be assessed by the researcher and specialist to determine whether they are exercise-related. If patients feel unwell during participation in the intervention, they will receive prompt and appropriate treatment.

### Strategies to improve adherence to interventions {11c}

Adequate pre-intervention education was provided to patients in the trial group.The assessment of all patients will be completed within a week and will not take up too much time.

### Relevant concomitant care permitted or prohibited during the trial {11d}

In the “Eligibility criteria {10}” section, subjects cannot participate in other sports training programs during the trial.

### Provisions for post-trial care {30}

Details of the operation are in the “Criteria for discontinuing or modifying allocated interventions {11b}” section. Additionally, enrolment into the study ensures patients are duly protected against negligent harm through standard National Health Service (NHS) indemnity arrangements.

### Outcomes {12}

Participants will be assessed within 1 week of admission at baseline and the end of 4 weeks. The primary outcome is the 10 m maximum walking test (10MWT). Secondary outcome measures include the limits of stability test (LOS), Berg balance scale test (BBS), Functional Ambulation Categories test (FAC), Timed Up and Go test (TUG), trunk impairment scale test (TIS), ultrasound indicators of the diaphragm and transversus abdominis (UI), rhythmic weight shift test (RWS), walk across test (WA), Fugl-Meyer assessment of lower extremity (FMA-LE), and Barthel index of ADL test.

### Participant timeline {13}

Details of the timeline are in Fig. 2.

### Sample size {14}

The study was a randomized controlled trial, with the 10 m maximum walking speed of the study participants as the main outcome indicator observed. The study was found by sample estimation with the G*Power 3.1 software, which, combined with previous studies, resulted in an effect size of 1.1327272, a power value of 0.9, and a significance level of *a* = 0.05, giving a sample size of 36 cases. Considering that there may be a 15% attrition rate during the trial, the required sample size was obtained. The final sample size was calculated to be 42 cases.

### Recruitment {15}

Following the proposed timeline, patient recruitment for this study will commence on September 1, 2022, and will continue until 1 year later or until the desired sample size is achieved. As this is a single-center clinical trial with a clear patient source, we will collect patients who meet the recruitment requirements from the hospital medical record system based on inclusion and exclusion criteria. To facilitate effective communication with patients, a comprehensive plan and methodology will be developed, which includes obtaining informed consent and conducting a video presentation explaining the study’s objectives and procedures. In addition, we will explain to subjects the advantages and disadvantages of the treatment and the relevant safety measures to be taken during the trial. Based on the recruitment criteria, the study team will initially estimate the likelihood of inclusion for each subject and, after the subject has signed the informed consent form, will carry out the relevant tests to confirm whether the subject conforms to the inclusion/exclusion criteria.

## Assignment of interventions: allocation

### Sequence generation {16a}

Details of the operation are in the “Trial design {8}” section.

### Concealment mechanism {16b}

Details of the operation are in the “Trial design {8}” section.

### Implementation {16c}

Details of the operation are in the “Trial design {8}” section.

## Assignment of interventions: blinding

### Who will be blinded {17a}

Details of the operation are in the “Trial design {8}” section.

### Procedure for unblinding if needed {17b}

If the following events occur during the trial, blinding will be lifted.:If the safety monitoring committee or data monitoring committee identifies an evident safety concern based on trial data that necessitate modifications to the trial or control group, or discontinuation of the trial, appropriate action will be taken.Immediate intervention will be warranted if a participant enrolled in the trial reports an apparent adverse reaction or side effect to the drug being tested.The results of the primary endpoint indicator of the trial have been sufficiently demonstrated that continued blinding is not required.

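### The unblinding rule would lift blinding mid-trial on an undefined efficacy result without protecting the outcome assessor, the only blinded party; at the planned interim this would expose mainly 6-month evaluations

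*Protocol article*

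**What the plan says.** Procedure for unblinding if needed {17b} opens with an affirmative rule: "If the following events occur during the trial, blinding will be lifted". Three events follow.

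- A safety concern identified by the safety or data monitoring committee.
- An adverse reaction in a participant: "Immediate intervention will be warranted if a participant enrolled in the trial reports an apparent adverse reaction or side effect to the drug being tested".
- An efficacy result: "The results of the primary endpoint indicator of the trial have been sufficiently demonstrated that continued blinding is not required".

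The third event has no threshold and no named decision-maker. The section nowhere limits whose blinding ends.

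Trial design {8} says who is blinded: "it will be difficult to conceal the grouping from the therapist and subjects, but it will be possible to blind the outcome indicator measurer". It adds: "We will arrange for a new assessor to replace the assessor familiar with allocation to achieve single blinding". The Discussion, in its list of measures against bias, commits to separate staff for randomisation and outcome assessment so that single blinding is kept.

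Three further sections bear on timing. Trial design {8} plans "a final assessment post-trial, and a follow-up evaluation six months later". Outcomes {12} names only baseline and the end of 4 weeks, with the 10 m maximum walking test as primary outcome. Interim analyses {21b} plans one look at the primary endpoint, once half the patients have completed 6 months of follow-up. A statistician does the analysis and presents it to the DMC.

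**The concern.** Therapists and patients know the allocation, so the only blinding described that could be lifted during data collection is the assessor's. Ending it because the treatment appears to work serves no evident purpose. The DMC can review results by arm without the assessor hearing of them, and a convincing early result is no reason to inform the person still measuring patients.

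Assessor blinding is the safeguard against detection bias on which the Discussion relies. A walking test at maximum speed and rater-scored scales such as the Berg balance scale, the trunk impairment scale and the Fugl-Meyer assessment can be influenced by encouragement and scoring. That is my judgement of these measures; the article itself describes the walking test as objective. If the rule operated while assessments were outstanding, the data would be part blinded and part unblinded, and the unblinded part would come from an assessor who might also know that the new training had already been judged effective.

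**Working it through.** **Plan's own figure.** Sample size {14} gives effect size 1.1327272, power 0.9, alpha 0.05, 36 cases, and 42 after 15% attrition. A two-sided two-sample t-test gives power 0.893 with 17 per arm and 0.910 with 18 per arm, so 36 reproduces. For attrition, 36 × 1.15 = 41.4, rounded up to 42 (36 / 0.85 = 42.4 would round up to 43). The point does not turn on this difference; 42 is used below.

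**What would remain at the planned interim?**

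Inputs from the article: 42 patients; recruitment for up to 1 year or until the target is reached (Recruitment {15}); primary test at 4 weeks; interim when 50% (21 patients) have completed 6 months of follow-up.

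Assumptions: uniform accrual over *A* = 6, 9 or 12 months; no dropout; unblinding on the day the interim condition is met (any delay lowers the counts). The article does not say whether the 6 months run from randomisation or from the end of treatment, so both are shown.

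Patient *i* enters at month *t* = (*i*/42) × *A* and has the 4-week test at *t* + 28/30.4375 = *t* + 0.92. The interim falls when patient 21 completes follow-up.

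| 6 months counted from | *A* (months) | Interim at month | 4-week tests outstanding | 6-month evaluations outstanding |
|---|---|---|---|---|
| Randomisation | 6 | 9.0 | 0 | 21 |
| Randomisation | 9 | 10.5 | 0 | 21 |
| Randomisation | 12 | 12.0 | 4 | 21 |
| End of treatment | 6 | 9.92 | 0 | 21 |
| End of treatment | 9 | 11.42 | 0 | 21 |
| End of treatment | 12 | 12.92 | 0 | 21 |

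Check of the row with 4: patient 21 enters at 6.0 months, so the interim is at 12.0. A 4-week test is outstanding if *t* > 12.0 − 0.92 = 11.08, that is *i* > 38.8, which leaves patients 39 to 42.

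**Size of the shift.** If a fraction *f* of patients, balanced across arms, is assessed unblinded, and that moves the between-group difference among them by *b* SD, the pooled difference moves by *f* × *b*. The article gives no value for *b*; I assume 0.2 to 0.5 SD.

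- Four-week primary test, planned interim: *f* runs from 0 to 4/42 = 0.095. The shift is 0 at the low end and, at the high end, 0.095 × 0.2 = 0.02 to 0.095 × 0.5 = 0.05 SD. Against the planned effect of 1.13 SD, 0.05 is about 4%.
- Six-month evaluation, planned interim: *f* = 21/42 = 0.5, so the shift is 0.5 × 0.2 = 0.10 to 0.5 × 0.5 = 0.25 SD for any susceptible measure taken at that visit.
- Earlier trigger: *f* for the 4-week test rises with the number of patients not yet tested. The rule in {17b} is not tied to the interim, but no earlier look is planned.

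**The case against.** The best defence is that the rule is conditional and its wording loose. It applies only if the result is so well established that blinding is no longer needed, and it does not say that the assessor is told. The only planned look goes from a statistician to the DMC, and nothing in Interim analyses {21b} sends results by arm to the assessor. The Discussion commits to keeping single blinding. This stands as a limit on likelihood and size. It does not rescue the rule, because {17b} says that blinding will be lifted and the assessor is the only blinded party described.

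A reader might infer that half of the primary data would be collected unblinded, with a shift of 0.10 to 0.25 SD in the primary effect. The documents do not support that. The planned interim comes so late that few or no 4-week tests would be left; the half-exposed figure fits only the 6-month evaluation. Nor does the text establish which tests are done at that visit: Outcomes {12} stops at 4 weeks, Trial design {8} speaks of treatment effectiveness without listing measures, and the schedule figure is not available to me.

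A reader might also take the adverse-reaction condition to unblind the whole trial. Its sentence speaks of immediate intervention for a participant, and an ordinary reading would confine any unblinding to that one person. The text is ambiguous. The mention of a drug is a slip that changes no analysis.

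**Conclusion.** The point holds as a conditional defect. {17b} contains an efficacy trigger for lifting blinding during the trial, with no threshold and no protection of the assessor, and this conflicts with the single blinding set up in Trial design {8} and relied on in the Discussion. It is a rule stated in the text, so this is more than a detail left to another document.

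Its likely effect on the primary outcome is small: about 0 to 0.05 SD if the trigger follows the planned interim. The larger exposure, 21 of 42, is at the 6-month evaluation. These figures rest on uniform accrual over 6 to 12 months and on an assumed bias of 0.2 to 0.5 SD that has no source in the article. An earlier trigger, which the wording allows, would expose more primary tests. No sample-size figure changes.

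**What to change.** In Procedure for unblinding if needed {17b}:

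1. Delete the efficacy trigger.
2. State that outcome assessors stay blinded until the last assessment of the last patient is done and the database is locked.
3. State that interim results by arm go only to the statistician and the DMC. This makes explicit what Interim analyses {21b} nearly says already.
4. Reconcile the adverse-reaction condition with Criteria for discontinuing or modifying allocated interventions {11b}, under which the therapist records events and the researcher and specialist assess them. Say whether the condition concerns one participant or the whole trial, and correct the reference to a drug, since this is an exercise trial. How adverse events are managed is for the investigators to settle.

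The cost is protocol wording. No assessment, sample size or analysis changes. The first three items need no change to how adverse events are handled.
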